### Study design and group allocation

This study is conducted as a randomized controlled trial with two active treatments: TAU + EFT and TAU. A 2 × 3 design is used with one between-subject factor (two treatment conditions) and one within-subject factor (time: pre, post, 12 month follow-up).

After completion of the baseline assessment and checking of the inclusion and exclusion criteria, a randomization procedure with equal allocation of patients to each treatment condition is used. To ensure a balanced distribution of diagnostic groups in the two treatment arms, a stratified randomization is applied. The allocation lists are created by an independent researcher with a computerized random number generator and are unknown to the investigators. The study design is shown in Fig. 1.

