## Methods

### Participants

A total of 130 patients fulfilling the diagnostic criteria for a unipolar depressive (ICD, F32), anxiety (ICD, F40, F41) or adjustment disorder (ICD, F43.2) are being recruited, with 65 participants randomly assigned to the TAU + EFT condition and 65 to treatment as usual. Participants are recruited at the psychotherapy outpatient clinic of the University of Bern, once they have registered for therapy and meet the requirements for participation in the study. As both conditions can be offered as treatments with empirically supported effects, it is not expected that many patients will decline, although the standard of 25 ± 3 sessions may be an obstacle to some.

With an average of three therapies per therapist, 23 therapists are needed per condition. In support of external validity and generalizability of our findings, therapists of varying experience are included. The participation of five experienced therapists and 18 therapists in training per condition is planned. All therapists in this study have a master’s degree in psychology and therapists in training have been in postgraduate training at the University of Bern for at least 1 and a half years.

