### Sample size calculation

Based on a power analysis with G*Power [25] an optimal total sample size of 130 patients allows for the detection of a small effect (Cohen’s f = 0.10) for the interaction between time (pre, post, follow-up) and treatment condition (TAU + EFT vs. TAU) (repeated measures analyses of variance (ANOVA), within-between-interaction; *α* = 0.05; power = 0.80; number of groups = 2; number of measurements = 3; pre-post correlation of pre-post values: *r* = 0.6; non-sphericity correction = 1). Multilevel models allow for assessment-by-assessment approaches: Assuming 130 patients and three assessments per patient (pre, post, follow-up), the resulting N would be 390. Further assuming a 20% dropout rate at follow-up, this sample would be reduced to 312. This would enable the detection of small effects of 3.4% explained variance in a regression model (linear multiple regression: random model; H1: ρ2 > 0; α = 0.05; power = 0.80) with three predictors (treatment condition, time, and their interaction); and would still allow the identification of small effects of 5.1% explained variance in a model including additional covariates with a total of ten predictors [25].

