### Analysis

Baseline descriptive statistics will be generated for all randomized patients and compared between the two study arms with ANOVA (for continuous variables) and χ2 statistics (for categorical variables). Missing values will be substituted with the procedure of multiple imputation. The research questions will be examined with the appropriate multilevel approaches, mainly two-level regression and growth analyses. These approaches take into account non-independence of observations in repeated measures outcome and the different number of sessions attended by the patients. Furthermore, we intent to test potential variability within therapists based on a longitudinal three-level model. The primary outcome analysis will be a modified intention-to-treat analysis that includes all patients who were randomized and attended at least one therapy session. These analyses will compare treatment differences in continuous outcome variables over time for TAU + EFT and TAU. Separate multilevel analyses will be run for the primary and each of the secondary outcome variables across three time points (pretreatment, post- treatment, 12-month follow-up). We expect primary and secondary outcome measures to be highly inter-correlated loading on one outcome factor [34]. For the purposes of the present study, a standardized composite measure taking primary and secondary symptom-related, self-report measures into account will be reported. Models will be run assuming random intercepts and slopes. For the main research questions, level-one models of individual change over time and level 2 models for the between-subjects factors are conducted. Each analysis will examine the overall effect of change over time (time), the difference between TAU + EFT and TAU, and the differences in changes over time by condition as a cross level interaction. To assess maintenance of gains, the multilevel regression analyses will be repeated with just the post-treatment and follow-up time points. A secondary series of analyses will include only those patients who completed the originally allocated treatment. Mechanisms of change will be examined as mediation effects in multilevel regression and structural equation models. Moderator effects will be analyzed as cross level interactions. Therapist effects will be investigated in three-level models. Multiple regression models will be used to predict residual change in the composite score between post and follow-up, by the level of structural change at post-treatment.

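### The primary model leaves the arms' baseline means free to differ; a common baseline or a baseline covariate would cut the variance of each later arm contrast by 20% at the plan's own r = 0.6, and the diagnostic strata should be named in the same edit

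*Protocol article*

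**What the plan says.** The section Study design and group allocation places the baseline assessment before randomisation and says "To ensure a balanced distribution of diagnostic groups in the two treatment arms, a stratified randomization is applied". It describes a design with a single between-subject factor, the treatment condition.

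The Analysis section runs the outcome models over pretreatment, post-treatment and 12-month follow-up. Each model is to examine change over time, the difference between the arms, and "the differences in changes over time by condition as a cross level interaction". It also mentions level-2 models for between-subject factors, without listing those factors.

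The Sample size calculation section uses the same structure. The total of 130 is computed "for the interaction between time (pre, post, follow-up) and treatment condition (TAU + EFT vs. TAU", and the regression version is described "with three predictors (treatment condition, time, and their interaction". The same sentence goes on to a ten-predictor model with further, unnamed covariates.

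**The concern.** Baseline precedes allocation, so the randomised arms have the same expected baseline mean and any observed difference there is chance. A model with pretreatment among the outcomes and an unconstrained condition term estimates that chance difference and subtracts it from every later difference. The estimate stays unbiased but carries avoidable noise.

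The condition main effect is also awkward to read. Depending on how time is coded, which the article does not fix, it can be the pretreatment difference itself or an average that includes a visit where treatment cannot have acted.

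Diagnostic group was considered important enough to stratify on, yet no outcome model names it. Precision is at stake: the sample size has almost no margin over 80% power, and the Discussion acknowledges that comparable trials found no great differences.

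**Working it through.** **Inputs.** From Sample size calculation: N = 130, f = 0.10, r = 0.6, non-sphericity correction 1, "within-between-interaction; *α* = 0.05; power = 0.80", "number of groups = 2; number of measurements = 3". From Participants: 65 per arm. The working below assumes complete data, unit SD, and the equal correlation between visits that a single r with correction 1 implies.

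**1. The plan's own figure.** For the repeated-measures interaction, λ = N·m·f²/(1−r) = 130 × 3 × 0.01/0.4 = 9.75, with df 2 and (130−2) × 2 = 256. Power is 0.8001. At N = 128 it is 0.793, so 130 is the smallest total that reaches 80%. The figure reproduces.

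**2. Variance of one arm contrast (post or 12 months).**
- Free baseline (change): (2/65) × 2(1−0.6) = (2/65) × 0.80 = 0.0246; SE 0.157.
- Common or adjusted baseline: (2/65) × (1−0.6²) = (2/65) × 0.64 = 0.0197; SE 0.140.
- Ratio: 0.64/0.80 = (1+r)/2 = 0.80. The variance is 20% lower and the SE 10.6% lower.
- Difference detectable with 80% power: 0.44 SD falls to 0.39 SD.

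**3. Power of the 2-df interaction.** The post and 12-month contrasts have covariance (2/65) × [0.80, 0.40; 0.40, 0.80] with a free baseline and (2/65) × [0.64, 0.24; 0.24, 0.64] with a common one. Each effect pattern below is scaled to f = 0.10, so the free-baseline λ is always 9.75 and power 80.0%. The same df are kept for the common-baseline model, as an approximation.

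| Effect pattern (pre, post, 12 months; SD) | λ, common baseline | Power at N = 130 | N for 80% |
|---|---|---|---|
| 0, 0.424, 0.424 | 13.30 | 91.1% | 96 |
| 0, 0.245, 0.490 | 12.41 | 89.0% | 104 |
| 0, 0.424, 0 | 10.64 | 83.5% | 120 |

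Check of the first row: 65/2 × 2 × 0.18/(0.64+0.24) = 13.30, against 65/2 × 2 × 0.18/(0.80+0.40) = 9.75.

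**4. Sensitivity.** For r from 0.3 to 0.8 the single-contrast variance ratio runs from 0.65 to 0.90. With linear time over three equally spaced points, the ratio for the slope difference at r = 0.6 is 0.786, so the gain does not depend on categorical time. For the post-to-follow-up maintenance contrast the ratio is 1.00, so there is no gain.

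**5. Strata.** The document does not say how much outcome variance diagnosis explains. If it explained 0, 2, 5 or 10% of the variance of the tested contrast (assumed range), modelling it would lower that variance by the same share, worth about 0, 3, 7 or 13 of 130 patients (130 × share). In a complete, balanced free-baseline model, a stratum main effect alone leaves the time-by-condition estimate essentially unchanged. The gain needs the stratum-by-time term, or the baseline change made at the same time.

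**The case against.** The strongest reply is that nothing here is an error. The research question concerns change from pre to follow-up, the model tests a difference in change, and the sample size was computed for that same interaction. The cost of the free baseline is thus already paid for in N = 130. This stands, and it is why the point is about efficiency.

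A reader might go further and infer that the analysis ignores the strata, with an inflated SE and a distorted type I error as established facts. The document does not support that. It leaves room for unnamed covariates and unlisted between-subject factors, it is a condensed article, and a covariate list may sit in an analysis plan that is not shown. Nor does it give any basis for how prognostic diagnosis is for a composite of three symptom scales. Differences between strata in level cancel from a comparison of change; only differences in course would matter.

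It is also fair that the change is not entirely free. Stratum terms use a few degrees of freedom. The analysis set requires at least one attended session, an exclusion after randomisation that slightly weakens the equal-baseline argument. The reading of the condition main effect depends on time coding: with time zero at a later visit, it is the arm difference at that visit.

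**Conclusion.** The baseline point holds as an improvement in efficiency. At the plan's r = 0.6, a common or adjusted baseline lowers the variance of the arm contrast at each later visit by 20% and raises power at f = 0.10 from 80% to about 84-91%. These figures rest on complete data and equal correlations; with random slopes or dropout they would differ, and a higher r would shrink the gain.

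The plan as written is unbiased and meets its stated power, so inferring a biased effect or a wrong sample size would go too far. On the strata, the document supports only that diagnostic group is not named in the outcome models. Omission would tend to make the test slightly conservative, by an amount that cannot be computed from the document.

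**What to change.** In the Analysis section, specify a constrained longitudinal model in which the arms share one pretreatment mean, or a model with the baseline score as covariate and post-treatment and 12-month follow-up as outcomes. Report the arm differences at those two visits in place of a condition main effect that involves the pretreatment visit. In the same edit, name diagnostic group and diagnostic group by time as fixed effects, or confirm that they are already among the unnamed covariates.

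The cost is analysis wording and a few degrees of freedom; baseline scores and diagnoses are already collected. The change should be fixed before outcomes are compared by arm. The article reports 28 of 130 patients recruited in November 2016.

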**Fig. 1 Fig1:**
[figure not shown]
Participant recruitment and study flow chart

### Description of the interventions

The treatment conditions are Psychological Therapy as usual and Psychological Therapy with emotion-focused components. Each intervention consists of 25 ± 3 sessions of 50 min each. Twenty-five sessions is the official standard for short-term therapies in the German health-care system. To standardize the duration to some extent serves to facilitate the comparison of therapies in the planned process analyses.

*Case formulation and Plan Analysis:* Both treatments are based on Psychological Therapy [5], an integrative form of cognitive-behavioral therapy and are based on explicit individual case formulations. The case formulations include an analysis of the individual etiology for the development and maintenance of patient problems. A first overarching question is which factors lead to inconsistency (i.e., the tension resulting from discrepancies between needs and reality and from internal conflicts [4]). Inconsistency has been shown to be closely related to mental problems [26]. Second, patient strengths and resources are emphasized and used (e.g., abilities, preferences, favorable circumstances, etc.). The patient’s ability to secure and enhance consistency and to solve problems is conceptualized in terms of Plan Analysis [27]. The case formulation also includes an analysis of problems and potentials for the therapeutic relationship.

Psychological therapy further makes reference to general change factors, and an explicit prescriptive concept for fostering the therapeutic relationship (Motive-Oriented Therapy Relationship as derived by the therapist from Plan Analysis). The main focus of Plan Analysis [27] is the instrumentality of behavior and experience (what conscious or non-conscious purpose does an aspect of overt or covert behavior hypothetically serve?). From the patient’s verbal and nonverbal behavior, the therapist infers underlying Plans of which many are non-conscious. For a specific patient, the therapist defines and implements a customized therapeutic relationship offer based on an individual Plan Analysis. Whereas the Motive-Oriented Therapy Relationship is a prescriptive approach, it is neutral in terms of therapy orientations. Its essence is to recognize, support and foster a patient’s positive motives in an active way that is not contingent to the presenting problem behaviors. Whereas the therapeutic procedure is developed individually, it utilizes etiological models and therapeutic procedures as often described in manuals. Following the principles of General Psychotherapy, the choice of helpful concepts and interventions is generally free, but empirical evidence is a strong argument for the therapist to favor one over another. In principle, all change factors, clarification, resource activation, problem activation, and problem mastery [4], are utilized, and the whole range of broad-spectrum behavior therapy interventions may be implemented [28–30]. However, it has been found in the past that working with emotions (instances of the change factors problem activation and clarification) has normally less weight in comparison to more cognitive/rational forms of clarification, skill building, or behavioral exercises. As explained above, this is closely related to lesser familiarity with and a greater insecurity in the implementation of interventions focusing on emotions.

*Treatment as usual with emotion-focused components* [8] is based on Psychological Therapy, but emphasizes working with emotions, particularly the use of EFT models and techniques. This involves the practice of mainly four psychological skills: empathy, focusing, two-chair work and empty-chair work. These are conveyed in a special 8-day training and supported by supervisions (individually or in small groups of up to four supervisees) on average every 2 weeks, so that therapists feel comfortable using them. In addition every 3 months a supervision of the supervisors by expert EFT supervisors takes place. Manuals, which are relatively heuristic/flexible to allow for individualized procedures, accompany instructions for the interventions. All components of both interventions must be implemented according to the manual’s specification. For detailed information on the content of EFT-components see Table 1.

**Table 1 Tab1:** Content of the emotion-focused components

EFT-Component	Content
Empathy	Empathy forms the basis of the therapeutic work in emotion-focused therapy as a technique and the fundament of the therapeutic relationship. Different forms of empathy play an important role in the shaping of the therapeutic relationship, affect regulation, deconstruction and the establishment of positive behavior towards the self.
Focusing	Focusing is a therapeutic technique to help expand the cognitive memories by the corresponding bodily reactions and thereby activate affective schemes usually arising in problematic situations. The goal is to look at current behavior in a larger context and recognize potential relationships to past experiences.
Two-chair work	The two-chair dialogue is used for confrontational processes e.g. self-evaluative splits, anxiety-splits and hopelessness splits where the patient operates alternating from both chairs. The main aim of two-chair work is an increase in self-compassion.
Empty-chair work	An indication for the empty-chair work is unfinished business with a significant other. The significant other can be imagined in the empty chair and contacted. The objective is a change in emotional schemes concerning the significant other.

*Treatment as usual:* In an add-on design, it would be problematic to give special training and attention to therapists only in one condition, because it would be hard to retrospectively single out factors such as higher expectancy, additional investment of time, allegiance, etc. To ensure that effects are specifically attributable to the add-on condition, it is important to balance out the conditions by making an equivalent addition also to the TAU condition, while keeping these additions within the concepts that characterize TAU. Thus in the TAU condition, self-regulatory processes as conceptualized by Carver & Scheier [31] and others receive particular attention as an equivalent addition. Self-regulatory processes are part of the consistency theory described by Grawe [4] and are conceptually part of Psychological Therapy as usual. It has been found though, that therapists seldom exploit the concrete possibilities of utilizing the self-regulation perspective in practice. Therefore, concrete self-regulation based interventions including psychoeducation on self-regulation models have been described and conveyed in the training. The self-regulation perspective does not come along with specific interventions. However, the self-regulation perspective determines the planning of interventions in this condition, the way therapists are conveyed to their patients, and the choice of an attention focus.

In addition, therapists in this condition are advised to use strategies emphasizing emotions not more than considered necessary based on the individual case conceptualization. The first category in Table 1, empathy, is considered to be part of TAU, although plausibly more typical and frequent in the TAU + EFT condition. Techniques most typical for EFT (categories 2–4 in Table 1) are proscribed although in the improbable case that a therapist thinks, that an intervention typical for EFT is absolutely required for a particular patient, he or she can argue in favor of such an intervention vis a vis the supervisor who can approve it, if convinced that no non-EFT procedure would lead to similar effects.

The amount of training and supervision is equivalent in both conditions. Besides the basic model of self-regulation by Carver & Scheier [31] other concepts are part of this active control condition, e.g. practicing an inner monologue for the planning and regulation of behavior [32] and clarification which factors lead to maladaptive self-organization, in particular ego depletion [33]. For a detailed description of the self-regulation components see Table 2.

**Table 2 Tab2:** Content of the self-regulation components

SR-Component	Content
Explanation of the SR-model	Explanation and discussion of the basic model of self-regulation. Illustration of both, self-regulatory and self-organized processes. Responding to the different boxes in the model and development of possible therapeutic starting points.
Clarification, when the patient produces perceptions, instead of objective change	Identification of changes reducing discrepancies between desired and the perceived states in perception only, as opposed to more tangible, concrete changes.
Deliberate reflection of goals and values	Goals, values, needs and standards are brought to mind and reflected. Finding out possible meanings for the activity of the comparator (which compares perceived to desired states).
Tracing the development of ideals and norms from personal history	Clarification of the origin of goals, values, needs and standards from the biography of the patient.
Attention-regulation	Training of conscious adaptation of the allocation of attention to the requirements and the switching between different modes of perception (deliberate/conscious vs. implicit/self-organized). Focusing attention on self-organized patterns of attention.
Work on self-instruction	Practicing self-control by the concretization of long-term consequences, to strengthen them over short-term consequences.
Regulation of behavior	Learning to monitor and control own behavior in terms of dual-process models (deliberate vs. self-organized regulation).
Regulation of the body	Relaxation exercises and techniques to reduce tension and agitation.
Emotion-regulation	Training of skills in emotion regulation as part of self-regulation.

### Measurements

For an overview of assessments at baseline, intermediate measurements (8 weeks, 16 weeks), post-treatment after 25-weeks, as well as 6, 12 and 36 month follow-up see Table 3.

**Table 3 Tab3:** Measurements and time of assessment

Instrument	Abbr.	Aim	Time of assessment
Clinician administered			
Structured Clinical Interview for DSM IV	SCID	DSM-IV Axis I/II disorders	pre, post
Hamilton Depression Rating Scale	HDRS	severity of depressive symptoms	pre, post
Goal Attainment Scaling	GAS	individual goals	pre, intermediate, post
Self-report ratings			
A. Symptom severity			
Brief Symptom Inventory	BSI	symptom impairment	pre, intermediate, post, follow-up
Beck Depression Inventory	BDI-II	severity of depressive symptoms	pre, intermediate, post, follow-up
Beck Anxiety Inventory	BAI	severity of anxiety symptoms	pre, intermediate, post, follow-up
B. Wellbeing			
World Health Organization 5	WHO-5	psychological wellbeing	pre, intermediate, post, follow-up
Short Form 12 of the Health Survey	SF-12	health-related quality of life	pre, intermediate, post, follow-up
C. Coping/Emotion regulation			
Self-assessment of Emotional Competences	SEK-27	dealing with negative emotions	pre, post
D. Interpersonal problems			
Inventory of Interpersonal Problems	IIP-32	interpersonal problems	pre, intermediate, post, follow-up
E. Motives/Incongruence			
Inventory of Approach and Avoidance Motives	FAMOS	motivational goals and schemes	pre, post
Incongruence Questionnaire	INK	incongruence	pre, intermediate, post, follow-up
F. Process measures			
Bern Post-Session Report Patient Version	BPSR-P	treatment process	after every therapy session
Bern Post-Session Report Therapist Version	BPSR-T	treatment process	after every therapy session
Symptom Checklist	SCL-9	psychological distress	after every therapy session
Classification of Affective Meaning States	CAMS	emotional processing	rating of therapy session
Experiencing Scale	EXP	experiencing	rating of therapy sessions

*Abbr.* Abbreviation

